## **9.2. Storage and Transportation of Vaccines**

The study vaccine and placebo should be stored and transported at 20 ( $\pm 5$ ) °C. The storage temperature needs to be monitored and recorded daily. On the premise of maintaining automatic temperature monitoring and alarm, the temperature shall be recorded according to the specific conditions of the study site on holidays. If the storage and transport process is out of the specified temperature range, the site study pharmacist should immediately isolate the over-temperature study vaccine at -20 ( $\pm 5$ ) °C, contact the sponsor and the study monitor, and not use the study vaccines which experienced temperature excursion until advice is received from the sponsor on how to proceed.

## **9.3. Route of Vaccination and Immunization Procedure**

Site and route of administration: The site of administration is the lateral deltoid muscle of the upper arm, and the route of administration is intramuscular injection.

Immunization procedure: The participant assigned to the study vaccine group received 1 dose of the study vaccine on Day 0. The participants assigned to the placebo group received 1 dose of placebo on day 0.

## **9.4. Backup vaccine**

When the backup vaccine is needed in case of vaccine damage in the study, please refer to the corresponding SOP.

## **9.5. Vaccine number.**

The vaccine in this clinical study has a unique number in the format of 0001 and 0002.

---

## 9.6. Vaccine allocation

The study number will be assigned according to the enrollment order of the screened participants, and the screening number and the initials of the participants will be filled in the Randomization Table. The study vaccine or placebo will be obtained and administered according to the study number.

## 9.7. Vaccine packaging and labeling

The study label shall include the protocol number, the name of the study vaccine, the name of the company, the expiry date and batch number, the words For clinical research only, and the vaccine number, such as 0001,0002.

## 10. Concomitant medication:

**Concomitant medication:** Concomitant medication refers to all drugs other than investigational vaccines which are used from the day of vaccination to 28 days after vaccination, including antibiotics, antivirals, antipyretic analgesics, anti-allergy drugs, biological products (including vaccine, immunoglobulin, blood products, etc.), traditional (patent) medicine (except vitamins and/or food additives for non-therapeutic purposes), etc. Information on concomitant medications includes the name of the drug, dosage, administration date, and indication.

**Permitted medication:** During the study, participants should be allowed to take necessary medication in case of adverse events.

**Prophylactic drugs:** mean the drug given when there are no symptoms or anticipated occurrence of vaccination reactions. For example, If antipyretics are given for fever

---

prevention in the subjects without fever during the recruitment period, antipyretics are considered a type of preventive drug. If treatment with drugs is required due to the occurrence of an adverse event, there is no restriction. At enrollment, the participants are inquired about the ongoing drugs to confirm that antipyretics, analgesics, or anti-allergic drugs are not given.

**Permissible vaccines:** Only vaccines for emergency use (e.g., tetanus vaccine or rabies vaccine) are allowed within 28 days after vaccination. If any other vaccine is administered, it will be recorded and reported as a protocol violation. After the completion of the investigational vaccination, in case of emergency vaccination, the vaccine can be used according to the product instructions, and the safety should be closely monitored and recorded in detail. If the vaccination interval is less than 28 days, record and report a protocol violation.

**Recording of medication:** To assess the impact of medications used during the study on vaccine safety, or to collect all the adverse events that may be related to vaccination, the investigator must take measures to collect the medications taken by participants during the observation period. Safety information and concomitant medications will be collected from all participants of this study. Participants should be instructed to record all clinic visits and medications from the day of vaccination to 28 days after vaccination in the Diary Card and Contact Card, and the medications recorded by participants should be reviewed.

## **11. Study methods and procedures**

### **11.1. Participant Recruitment**

After the study sites are confirmed and approved by the IRB, IRB-approved advertisements will be distributed to any population who meets protocol requirements for age, vaccination history, and health condition.

---

## **11.2. Study procedure**

### **11.2.1. Visit 1 (Day 0)**

#### **(1) Informed consent and assignment of screening number**

The researcher needs to fully inform the participants about the clinical research information. If the participants accept written informed consent, then need to sign the ICF. The ICF shall be made in duplicate, one for the study site and one for the participant. After signing the ICF, the researcher will assign a screening number to the participant and make copies of the participant's identification materials.

#### **(2) Physical examination and screening.**

The researchers need to perform a routine physical examination of the participant who has signed ICR, observing the general condition, respiration, head and neck, lymph node, skin, etc., and take measures of their height, weight, axillary temperature, pulse, and blood pressure. Participants are required to provide a negative nucleic acid test report within 48 hours, and female participants of childbearing age are required to provide a negative pregnancy test certificate within 48 hours. Confirm the vaccination record of SARS-CoV-2 vaccines of the participant by checking the participant's health code, etc., and then determine whether the participant can be included in the clinical study according to the inclusion and exclusion criteria in combination with the inquiry records and measurement results.

#### **(3) Assignment of random numbers**

Participants who meet the inclusion criteria and do not meet the exclusion criteria as determined by the researcher through physical examination and consultation can be enrolled. The researcher shall fill in the Randomization Form with the initials and screening number of the enrolled participants, and sign the name and date; At the same time, assign a study number to the participant according to the enrollment sequence of the participant, and fill the study number in the Vaccination and

---

## Follow-up Record.

### (4) Blood collection before vaccination (only the immunity subgroup)

Blood collection for humoral immunogenicity test: about 5.0 mL venous blood is collected from the participant with a procoagulant tube (containing only procoagulant), and the serum is separated according to the operating procedures and sub-packaged into cryopreservation tubes.

Blood collection for cellular immunity test: about 15.0 mL venous blood is collected from the participant with a heparin anticoagulant tube

### (5) Vaccination

The vaccine preparation personnel shall obtain the vaccine with the corresponding number according to the study number of the subject, check that the information on the label of the vaccine box and the inner label is correct and consistent, and confirm that the vaccine status is normal. The vaccinator shall check the study number in the participant's Vaccination and Follow-up Record to confirm that it is correct.

The vaccinator shall check the participant information again before vaccination for each subject. After checking, the skin of the lateral deltoid muscle of the upper arm of the subject shall be disinfected with 75% medical alcohol, and the vaccine after the skin is slightly dry. After completion of vaccination, the investigator shall fill in the vaccination time, vaccination site, and other information in the corresponding position in the Vaccination and Follow-up Record, and sign the name and time.

### (6) Safety observation after vaccination

All participants will be observed at the study site for at least 30 minutes after vaccination and adverse events will be recorded. Investigator should distribute the Diary Card, thermometer, and scale to the participants, train the participants on how to use the thermometer and scale to observe adverse events, and how to fill in the

---

Diary Card and make an appointment for the participants to return the Diary Card.

The investigator should highlight the investigator's phone number on the copy of the ICF and Diary Card to the participants and instruct them to contact the investigator immediately if they experience any signs, symptoms, or events requiring hospitalization that they consider serious after vaccination.

#### **11.2.2. Visit 2 (Day 7+2 after vaccination) (only the immunity subgroup)**

##### **(1) Blood collection**

Blood collection for humoral immunogenicity test: about 5.0 mL venous blood is collected from the participant with a procoagulant tube (containing only procoagulant), and the serum is separated according to the operating procedures and sub-packaged into cryopreservation tubes.

Blood collection for cellular immunity test: about 15.0 mL of venous blood is collected from the participant with a heparin anticoagulant tube.

##### **(2) Safety observation**

Collect concomitant medications, AE, SAE, AESI, and pregnancy events.

##### **(3) COVID-19 case observation**

Determine whether the participant presents with COVID-19-related signs or symptoms.

#### **11.2.3. Visit 3 (Day 14+7 after vaccination)**

##### **(1) Collection and review of Diary Card**

Participants return the Diary Card. The investigator should review and confirm whether the AE or concomitant medications are completely and correctly recorded in the Diary Card together with the participant, and instruct the participants to make corrections and supplements, then recycle the Diary Card.

---

(2) Blood collection

Blood collection for humoral immunogenicity test: about 5.0 mL venous blood is collected from the participant with a procoagulant tube (containing only procoagulant), and the serum is separated according to the operating procedures and sub-packaged into cryopreservation tubes.

Blood collection for cellular immunity test: about 15.0 mL of venous blood is collected from the participant with a heparin anticoagulant tube.

(3) Training and Issuance of Contact Card

Participants will be given a Contact Card and trained to record all AE and concomitant medications (if applicable) from 15 to 28 days after vaccination.

(4) Safety observation

Collect concomitant medications, AE, SAE, AESI, and pregnancy events.

(5) COVID-19 case observation

Determine whether the participant presents with COVID-19-related signs or symptoms.

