|                            |                                                                | V1                                              | V2 | V3  | V4  | V5  | V6   |
|                            |                                                                | D0                                              | D7 | D14 | D28 | D90 | D180 |
| Time Window                |                                                                | /                                               | +2 | +7  | +7  | +15 | +30  |
| 14                         | Distribution of contact cards                                  | /                                               | /  | X   | /   | /   | /    |
| 15                         | Review and Recall Contact Cards                                | /                                               | /  | /   | X   | /   | /    |
| 16                         | Adverse events                                                 | X                                               | X  | X   | X   | /   | /    |
| 17                         | Concomitant medication                                         | X                                               | X  | X   | X   | /   | /    |
| 18                         | Protective Effectiveness Visits
Routine and case monitoring | X                                               | X  | X   | X   | X   | X    |
| 19                         | SAE、AESI                                                       | X                                               | X  | X   | X   | X   | X    |
| 20                         | Pregnancy-related events                                       | X                                               | X  | X   | X   | X   | X    |
| 21                         | EOS &                                           | /                                               |    |     |     |     | X    |

\*: The participant's vaccination record information for the COVID-19 vaccine was confirmed by checking the health code, etc.

#: When the on-site visit coincides with the required telephone visit, no additional telephone visit will be conducted.

a: Immunogenic blood collection for immunized subgroup participants only.

b: Additional cellular immunity blood collection for immunized subgroup participants only.

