### **➤ Safety observation from 0 to 28 days after booster vaccination**

All participants will collect all adverse events occurring within 30 minutes after vaccination, solicited inoculation site (local) and non-inoculation site (systemic) adverse events within 0-14 days, and unsolicited adverse events within 0 to 28 days.

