#### **11.4. Safety observation method**

##### **11.4.1. Safety observation time and method**

###### **(1) Within 28 days after vaccination**

Participants will be observed at the vaccination site for 30 minutes after vaccination. Investigators who have been trained and authorized need to systematically observe and measure the body temperature of each participant 30 minutes after vaccination, and record all AEs within 30 minutes after vaccination in detail. AEs will be observed and recorded through the Diary Card from 0 to 14 days after vaccination, and AEs will be collected and recorded through the Contact Card from 15 to 28 days after vaccination.

Investigators should check the original safety information of the Diary Card and Contact Card in time and input it into EDC after checking. Investigators should verify the name, duration, and severity of any AE and evaluate and determine its relationship to vaccination. Measures taken in response to the AE, combined treatment, and outcome of the AE, whether the event was a serious adverse event, and whether the event led to study discontinuation, must also be documented.

---

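### The Contact Card for days 15–28 is issued only at Visit 3, whose window runs to day 21, so up to 6 of its 14 days can pass before the participant has it

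*Protocol*

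**What the plan says.** - **Which card covers which days.** Protocol section 11.4.1 (1) states that "AEs will be observed and recorded through the Diary Card from 0 to 14 days after vaccination" and that "AEs will be collected and recorded through the Contact Card from 15 to 28 days after vaccination".
- **When the Contact Card is issued.** Section 11.2.3 (3), under Visit 3: "Participants will be given a Contact Card and trained to record all AE and concomitant medications (if applicable) from 15 to 28 days after vaccination". Row 14 of the Schedule of Activities (Table 1), "Distribution of contact cards", is marked at V3 only. At Visit 1, section 11.2.1 (6) hands out the Diary Card, thermometer and scale, but no Contact Card.
- **When Visit 3 takes place.** Nominally on day 14, with a window of +7 days (Table 1 and section 11.2.3), so from day 14 to day 21. At that visit, "Participants return the Diary Card".
- **What the cards must capture.** Section 6.7 calls for "unsolicited adverse events within 0 to 28 days". Section 10 has participants record "all clinic visits and medications from the day of vaccination to 28 days after vaccination in the Diary Card and Contact Card". Section 6.2.2 makes AE incidence within 14 and 28 days a secondary safety endpoint.
- **Other routes of collection.** Section 6.6 sets remote visits twice a week from day 7, and section 6.9 has AEs collected at them. Section 11.2.3 (4) collects AEs and concomitant medication at Visit 3. Section 11.4.1 (2) collects serious AEs (SAEs) and AEs of special interest (AESIs) for 6 months through remote visits and active reporting.

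**The concern.** The Contact Card is the participant's own running record for the second half of the 28-day period, but it reaches the participant on a date that may lie well inside that half. A participant seen on day 21 is fully compliant, yet is given, and trained on, a card for days 15–28 when days 15–20 are already past. Those days can then be entered only from memory or from what a remote contact picked up.

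The cards matter because section 11.4.1 has the investigators check the original safety information on them and enter it in the EDC. Mild unsolicited events, and the medication taken for them, are the entries most easily forgotten. How fully days 15–20 are recorded as they happen would therefore depend on where Visit 3 fell in its window, and the 28-day AE incidence could be somewhat understated.

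**Working it through.** The plan states no figure to reproduce. The check is a count of days.

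**Inputs**
- Contact Card period: days 15 to 28, so 28 − 15 + 1 = 14 days (sections 11.2.3 and 11.4.1).
- Visit 3 day v: 14 to 21 (Table 1 and section 11.2.3).
- Planned enrolment: 3,200 (section 6.5).

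**Formula.** Contact Card days that pass before the card is in hand = max(0, v − 15). The day of Visit 3 itself counts as covered.

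| Visit 3 on day | Days before issue | Which days | Share of 14 |
|---|---|---|---|
| 14 or 15 | 0 | none | 0% |
| 16 | 1 | 15 | 7% |
| 17 | 2 | 15–16 | 14% |
| 18 | 3 | 15–17 | 21% |
| 19 | 4 | 15–18 | 29% |
| 20 | 5 | 15–19 | 36% |
| 21 | 6 | 15–20 | 43% |

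The protocol's own rule for counting days between two dates (day 0 to day 4 counts as 3 days, in the synopsis definitions) also gives 6 days between day 14 and day 21.

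**Range over the trial.** If every Visit 3 fell on day 14 or 15, the total is 0 × 3,200 = 0 participant-days. If every one fell on day 21, it is 6 × 3,200 = 19,200. The document says nothing about the actual spread of visit dates, so only the range can be given.

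**Is the gap closed elsewhere?**
- No section extends the Diary Card past day 14, and none issues the Contact Card before Visit 3. Section 6.9 lists Visits 1, 3 and 4 for handing out and collecting the two cards without saying which card at which visit. Section 11.2.3 and Table 1 settle that.
- Visit 2 is for the immunogenicity subgroup only (section 11.2.2). The other 3,100 participants have no scheduled on-site visit between day 0 and Visit 3.
- At two remote visits per 7 days, a six-day gap holds about 6 × 2/7 = 1.7 contacts, so about two, each with AE collection under section 6.9. That sentence names AEs, SAEs, AESIs and pregnancy events, but not concomitant medication. Visit 3 collects both AEs and medication.

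**The case against.** The strongest reply is that little is really lost. Remote visits at a recommended 2–3 day interval mean that a participant is asked about AEs about twice within even the longest gap, so recall spans a few days rather than six. Visit 3 adds its own AE and medication review. The participant still holds the Diary Card until then. Participants are trained to report events promptly (section 12.3) and to call at once about anything they consider serious (section 11.2.1 (6)). Both arms follow the same card schedule, and participants and observers are blinded.

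Most of this stands, and it sets the limits of the point. A reader might infer that AEs on days 15–20 go uncollected. They do not: sections 6.9 and 11.2.3 provide for asking. A reader might also infer that the 14-day endpoint is affected. Late issue of a card that starts on day 15 cannot touch it. SAEs and AESIs have their own route. No bias between arms is shown, and the primary endpoint, sample size and type I error are not involved.

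One part of the reply does not stand. Having the Diary Card in hand does not close the gap, because its stated period ends on day 14 and no one is told to go on using it. Contacts every few days support recall; they do not replace an entry made on the day, least of all for medication, which section 6.9 does not list.

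A Visit 3 on day 14, or a Visit 4 on day 28, also cuts off the remaining hours of that day. This is a small matter, since the next remote visit can cover it.

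**Conclusion.** The point holds in a limited form. For any in-window Visit 3 on days 16 to 21, the stated record for days 15–28 arrives 1 to 6 days late, which is up to 43% of its period. The effect is confined to same-day recording of non-serious unsolicited AEs and concomitant medication on days 15–20. It bears on the completeness of the 28-day AE incidence and is expected to be similar in both arms.

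The trial-wide size lies between 0 and 19,200 participant-days. A single figure is tempting: visit dates spread evenly over the eight days would give 21/8 × 3,200 = 8,400. Nothing in the protocol supports an even spread, and no weight should be put on that number.

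The conclusion rests on the card periods, the issue point and the Visit 3 window being applied as written. It is of minor priority, but worth correcting because the correction is nearly free.

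**What to change.** 1. In section 11.2.1 (6), section 11.2.3 (3) and row 14 of the Schedule of Activities, move issue of the Contact Card and its training from Visit 3 to Visit 1, with use from day 15. Training on the Diary Card already takes place there, and Visit 1 is the only scheduled on-site visit before Visit 3 that all participants attend.
2. Add a reminder at a scheduled remote visit around day 14 to change from one card to the other.
3. Keep Diary Card review and collection at Visit 3 and Contact Card collection at Visit 4.
4. Where Visit 3 falls on day 14 or Visit 4 on day 28, confirm the rest of that day at the next scheduled remote visit. Leave the visit windows alone: opening Visit 3 on day 15 would shift the day-14 blood draw of the immunogenicity subgroup.

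The cost is that participants hold two cards from day 0, with a few extra minutes of training. No extra visit is needed, and neither the sample size nor the analysis changes.

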**11.2.4. Visit 4 (Day 28+7 after vaccination)**

(1) Collection and review of Contact Card

Participants return the Contact Card. The investigator should review and confirm whether the AE or concomitant medications are completely and correctly recorded in the Contact Card together with the participant, and instruct the participants to make corrections and supplements, then recycle the Diary Card.

(2) Blood collection

Blood collection for humoral immunogenicity test: about 5.0 mL venous blood is collected from the participant with a procoagulant tube (containing only procoagulant),

---

and the serum is separated according to the operating procedures and sub-packaged into cryopreservation tubes.

Blood collection for cellular immunity test: about 15.0 mL of venous blood is collected from the participant with a heparin anticoagulant tube.

(3) Safety observation

Collect concomitant medications, AE, SAE, AESI, and pregnancy events.

(4) COVID-19 case observation

Determine whether the participant presents with COVID-19-related signs or symptoms.

**11.2.5. Visit 5 (Day 90+15 after vaccination) (only the immunity subgroup)**

(1) Blood collection

Blood collection for humoral immunogenicity test: about 5.0 mL venous blood is collected from the participant with a procoagulant tube (containing only procoagulant), and the serum is separated according to the operating procedures and sub-packaged into cryopreservation tubes.

Blood collection for cellular immunity test: about 15.0 mL of venous blood is collected from the participant with a heparin anticoagulant tube.

(2) Safety observation

Collect SAE, AESI, and pregnancy events.

(3) COVID-19 case observation

Determine whether the participant presents with COVID-19-related signs or symptoms.

